## Specific Aims

The study aims to evaluate the benefit of 3D-printed models in preoperative patient education. We will recruit patients scheduled for colorectal surgery who present to the Vanderbilt University Medical Center Colorectal Clinic.

Aim 1: Investigate the effect of integrating a 3D model in patient-clinician interaction on patients' perception of shared decision-making. We will accomplish this by administering the validated Shared Decision-Making Questionnaire (SDM-Q-9) (Figure 1) among patients after their preoperative consultation and comparing the results of study cohorts (control vs. intervention arm).

Aim 2: Evaluating the change in anxiety and procedural-specific knowledge after incorporating a 3D model compared to standard care. To assess the change in anxiety, we will utilize the validated six-item State-Trait Anxiety Inventory questionnaire (STAI-6) (Figure 2). For evaluating a differential change in patient knowledge, we will use the Patient Education Assessment survey (Figure 3) and compare scores for two scales between the study cohorts.

Aim 3: Investigating the effect of health literacy on the outcomes of Aim 1 and Aim 2. We will categorize patients based on health literacy as described by the BRIEF: Health Literacy Screening Tool (Figure 4) and compare SDM-Q-9 score and the change in STAI-6 and Patient Education Assessment scores between the study cohorts.

Primary hypothesis: Patients educated preoperatively using 3D-printed models will perceive increased levels of shared decision-making, suffer lower procedural anxiety, and have an improved understanding of the procedure compared to standard care (using 2D images for patient education).

Secondary hypothesis: The primary hypothesis will be consistent across health literacy categories.

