## Trial Design

We will conduct a single-center pilot cluster randomized control superiority trial. Participating surgeons will be randomly assigned to either the control arm (standard care) or the intervention arm (3D-printed model) using the opaque sealed envelope method. Patients will be recruited in a cluster and study cohort, depending on the next available surgeon. A 1:1 enrollment ratio will be targeted (Figure 5). Blinding will not be performed.

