## Study Procedures and Data Collection

Recruitment: Surgical patients presenting to the colorectal clinic of a tertiary care hospital will be recruited during their preoperative visit.

Informed Consent: Patients who agree to participate in the study will be assessed to confirm eligibility and given a consent form from a clinic nurse or study investigator. All study-related questions will be answered before they agree to sign the written informed consent document, which will be recorded in the Research Electronic Data Capture (REDCap) database.

Study Visit: Surgical patients will be asked to complete the study questionnaires before their preoperative consultation (STAI-6 and Patient Education Assessment) before their consultation and SDM-Q-9, STAI-6, and Patient Education Assessment after the consultation at their preoperative consultation. These patients will only participate in the study during this visit and will not require any follow-up.

SDM-Q-9: This is a validated, nine-item self-report survey that measures how involved patients feel in the decision-making process with their healthcare provider . This survey will only be administered once, post-consultation (Figure 1).

STAI-6: This validated six-item tool  will be used to measure the patient's anxiety levels before and after the preoperative consultation to establish a baseline and understand how each intervention affects anxiety levels (Figure 2).

Patient Education Assessment: The 13-question survey aims to assess patients' knowledge and understanding of their colon anatomy, disease, procedure, and complication risks. This survey will be given both before and after informed consent to assess any changes (Figure 3).

The baseline demographic and clinical information of each patient will be collected by the research nurse at the preoperative visit, recorded in the institutional REDCap database, and compared between the study arms.

REDCap Data Entry: This project will utilize the REDCap electronic data capture tools hosted at Vanderbilt University Medical Center for data collection and management. REDCap will be used to capture all recruited patients who are enrolled in the study and store their individual data as well as study consent documentation.

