## Statistical Considerations

Sample size: Since we do not have prior data in this patient cohort to appropriately power or simulate our analysis, we used the mean and standard deviation of SDM-Q-9 in the literature [86.7 ( $\pm 11.6$ )]. To ensure that this study has adequate power to detect a clinically meaningful effect size and provide data for future studies, we assume a 5% risk of type I error and a 20% risk of type II error, a 1:1 enrollment ratio, and a targeted increase of 3 times the minimal clinically important difference ( $4^{17}$ ). This means that 20 patients needed to be allocated to each arm. Since this intervention has not been utilized in colorectal patients before, we target an expected rejection rate of 50%, meaning 80 patients should be approached (40 in each arm).

Data analysis plan: Patient characteristics will be compared between the 3D-printed model and standard care arms with the chi-squared test for categorical variables and the Student's t-test for comparisons between continuous variables. The postintervention SDM-Q-9, the preintervention and postintervention STAI-6, and the Patient Education Assessment Questionnaire scores will be compared between the study arms using the restricted maximum-likelihood estimation to account for the intraclass differences. The postintervention score will be treated as a dependent variable, while the preintervention score will be treated as a covariate. A similar subgroup analysis will be conducted after dichotomizing health literacy into adequate (17-20) and inadequate or marginal ( $<17$ ) groups. The level of significance will be at  $\alpha = 0.05$  throughout the manuscript. Statistical analyses will be performed using Stata (version 17, StataCorp LLC, College Station, TX). We do not plan on conducting any interim analysis.

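### The hypothesis of a consistent effect across health-literacy groups is matched to within-subgroup arm comparisons, which do not estimate the difference between subgroup effects

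*Protocol*

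**What the plan says.** Under Specific Aims, the protocol's secondary hypothesis is "The primary hypothesis will be consistent across health literacy categories". The primary hypothesis it refers to covers shared decision-making, anxiety and knowledge. Outcome Measurements repeats the consistency question for the change in knowledge score.

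The only analysis given for it is in the data analysis plan under Statistical Considerations. After describing the between-arm comparisons by restricted maximum likelihood, the text continues "A similar subgroup analysis will be conducted after dichotomizing health literacy into adequate (17-20", with scores below 17 as the second group. The 0.05 level applies throughout. No arm-by-literacy term, contrast between the two groups or criterion for consistency is named.

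On timing, Study Procedures and Data Collection says "Surgical patients will be asked to complete the study questionnaires before their preoperative consultation (STAI-6 and Patient Education Assessment", and then lists SDM-Q-9, STAI-6 and the knowledge survey for after the consultation. The BRIEF literacy tool is in neither list.

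**The concern.** Whether an effect is consistent is a question about the difference between two subgroup effects. An arm comparison repeated within each subgroup answers another question: is there an effect here, and is there one there? One subgroup below 0.05 and the other above it does not show that the effects differ, because the subgroups may simply differ in size. Both above 0.05 does not show that the effects agree, because both comparisons may be too small to find anything.

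At stake is the conclusion on Aim 3. A reader of the results could be told that the model works only for patients with adequate literacy, or that it works alike in both groups, when the data support neither statement. The primary comparison of the arms is not affected.

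**Working it through.** **Inputs from the protocol (Statistical Considerations).** SD 11.6; target effect 3 × 4 = 12 points, from "a targeted increase of 3 times the minimal clinically important difference" with that difference set at 4; "This means that 20 patients needed to be allocated to each arm".

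**Assumptions, not in the protocol.** Two-sided tests; literacy split 50/50, 70/30 or 80/20, the same in both arms; unadjusted SDM-Q-9; no clustering; subgroups independent.

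**The plan's own figure first.** n per arm = 2 × (z₀.₉₇₅ + z_power)² × 11.6² / 12².
- 80% power: 2 × (1.960 + 0.842)² × 134.56 / 144 = 14.7, so 15 (16 with the t distribution).
- 90% power: 2 × (1.960 + 1.282)² × 134.56 / 144 = 19.6, so 20.

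The stated 20 therefore corresponds to about 90% power, not the stated 80%. That is a separate matter. I take 20 per arm as given, which is the more favourable case here.

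**Power within a subgroup of n per arm.** Noncentral t with 2n − 2 degrees of freedom and noncentrality 12 / (11.6 × √(2/n)). For n = 10 this is 12 / 5.19 = 2.31, giving power 0.591. For n = 14, 6, 16 and 4 the power is 0.750, 0.367, 0.808 and 0.235.

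**Joint results when the true effect is 12 points in both subgroups.** With subgroup powers p₁ and p₂: both significant = p₁p₂; exactly one = p₁(1 − p₂) + p₂(1 − p₁); neither = (1 − p₁)(1 − p₂).

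| Split (n per arm) | Powers | Both | Exactly one | Neither |
|---|---|---|---|---|
| 50/50 (10, 10) | 59%, 59% | 35% | 48% | 17% |
| 70/30 (14, 6) | 75%, 37% | 28% | 57% | 16% |
| 80/20 (16, 4) | 81%, 24% | 19% | 66% | 15% |

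**Smaller common effects.**
- 8 points: exactly one significant in 43% (50/50) to 48% (80/20).
- 4 points, 50/50: power 0.113 in each subgroup, so neither is significant in (1 − 0.113)² = 0.79 and exactly one in 20%.

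**Six surgeons.** With a t reference on 4 degrees of freedom and an assumed intraclass correlation of 0 to 0.10, at 12 points both subgroups are significant in 9% to 18% and exactly one in 46% to 56%.

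**What an interaction estimate would offer.** SE = 11.6 × √(2/a + 2/b), where a and b are the per-arm subgroup sizes; half-width = t₀.₉₇₅ on 36 degrees of freedom (2.03) × SE.

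| Split | SE | 95% half-width | Power if the effects differ by 12 |
|---|---|---|---|
| 50/50 | 7.34 | 14.9 | 36% |
| 70/30 | 8.00 | 16.2 | 31% |
| 80/20 | 9.17 | 18.6 | 25% |

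The half-width exceeds the whole 12-point target at every split, before any allowance for clustering.

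**The case against.** The strongest reply is that the protocol states no rule for reading the subgroup results. It does not say that both groups must be significant, or that a split result means inconsistency. The phrase about a similar subgroup analysis does not mention separate tests, and subgroup estimates could be compared informally. An analysis plan that is not shown might add a contrast, and this is a secondary question in what the protocol calls a "single-center pilot cluster randomized control superiority trial".

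Part of this stands. Repeating the arm comparison in each group is the natural reading of a sentence that follows the between-arm analyses, but it is an inference. Three stronger readings that a reader might draw are not supported:

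- **That the groups will usually look inconsistent by chance.** At a 50/50 split a split verdict occurs in 48% of trials, and less often with smaller common effects. It passes half only near the planned effect with an uneven split, and the protocol gives no split.
- **That the plan gives the wrong answer most of the time.** That needs a both-must-be-significant rule, which the protocol does not contain.
- **That the cut at 17 is arbitrary, or that BRIEF is given after the consultation.** Appendix Figure 4 makes 17 the instrument's own threshold for adequate literacy, and the hypothesis is about categories. Nothing places BRIEF after the consultation, and the schema in Figure 5, which might show its timing, is not visible.

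What the reply does not remove is the mismatch. The protocol states a consistency hypothesis and itself names an analysis that does not estimate the quantity concerned. That is not a detail merely left for later.

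**Conclusion.** The point holds as a mismatch between hypothesis and analysis. It is worth correcting, but it does not threaten the primary comparison. The percentages describe SDM-Q-9 only and depend on the assumed literacy split and the absence of clustering. Corresponding figures for STAI-6 and knowledge, which are adjusted for the pre-consultation score, cannot be derived from the protocol. The risk runs both ways: split verdicts under an identical effect of the planned size, and two non-significant results when the common effect is small.

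The interaction model targets the right quantity but does not rescue the question. With about 40 patients the trial cannot establish consistency by that route either, and the protocol should say so.

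**What to change.** In the data analysis plan, replace the within-subgroup comparisons with one mixed model per outcome on all patients. Keep the clustering and baseline adjustment of the main analysis, and include arm, health literacy at the pre-specified cut of 17, and arm × literacy. Report the interaction and the arm effect in each literacy group, all with 95% confidence intervals. The continuous BRIEF score can be an optional sensitivity analysis; it uses more information but adds a linearity assumption in a small sample. Label the analysis exploratory and state that a non-significant interaction does not establish consistency.

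As a clarification, confirm in the study visit description that BRIEF is completed before the consultation, so that the groups are defined at baseline. One item asks about trouble understanding what one is told, which the consultation itself could influence.

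The cost is a few sentences of analysis text and one line on questionnaire timing. No extra patients, visits or questionnaires are needed.

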## Outcome Measurements

**Primary Outcome Measures:** The difference in the levels of shared decision-making using the validated SDM-Q-9 questionnaire (Figure 1) and the differential change in anxiety levels post-intervention using the validated STAI-6 questionnaire (Figure 2).

**Secondary Outcome Measures:** A differential change in the patient knowledge level captured by our 13-question Patient Education Assessment survey (Figure 3) and evaluating if the change is consistent when categorized by health literacy scores based on the BRIEF: Health Literacy Screening Tool (Figure 4).

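### Two primary outcomes are each tested at 0.05 with no rule on whether either or both must succeed, so the stated 5% type I error is not secured for the primary claim

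*Protocol*

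**What the plan says.** Protocol, Outcome Measurements, lists two primary outcomes without ranking them: "The difference in the levels of shared decision-making using the validated SDM-Q-9 questionnaire" and "the differential change in anxiety levels post-intervention using the validated STAI-6 questionnaire". Change in knowledge (Patient Education Assessment) is listed there as secondary.

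Protocol, Specific Aims, states a primary hypothesis with three parts: "Patients educated preoperatively using 3D-printed models will perceive increased levels of shared decision-making, suffer lower procedural anxiety, and have an improved understanding of the procedure". Understanding, which the outcome list makes secondary, is therefore part of the primary hypothesis. The three parts are joined by 'and', but the sentence is not presented as a rule for declaring success.

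Protocol, Statistical Considerations, sets the design error rates: "we assume a 5% risk of type I error and a 20% risk of type II error". The sample size uses one outcome only: "we used the mean and standard deviation of SDM-Q-9 in the literature", with "a targeted increase of 3 times the minimal clinically important difference". No standard deviation or target effect is given for STAI-6 or for knowledge. The data analysis plan then compares each score between arms and fixes a single level for all tests: "The level of significance will be at" α = 0.05. There is no split of alpha, order of testing, lead primary or requirement that both primaries succeed.

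**The concern.** Two primary outcomes, each tested at 0.05, keep a 5% error rate for the trial's primary claim only under some success rules. The protocol does not choose one.

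- If a significant result on either outcome supports the claim, the chance of at least one false positive exceeds the 5% stated in the same section.
- If both must be significant, the error rate is controlled, but the sample size says nothing about the chance of achieving both.

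Because the text does not decide, the choice could be made after the results are known. The trial is unblinded and the outcomes are self-reported, which gives more reason to fix the rule in advance. The three-part hypothesis adds to the uncertainty, because it leaves unclear which outcomes the primary claim covers.

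**Working it through.** **Inputs.** From Statistical Considerations: SDM-Q-9 standard deviation 11.6; target difference 3 × 4 = 12 points; type I error 5%; type II error 20%; 1:1 ratio; 20 patients per arm; α = 0.05 for every test. From Outcome Measurements: two primary outcomes. Assumed, because the protocol does not say: two-sided tests, and a correlation ρ between the two test statistics, tried from 0 to 0.9.

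**Step 1. The plan's own figure.** Per arm, n = 2 × SD² × (z₁₋α/₂ + z₁₋β)² / δ².

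- α = 0.05, 80% power: 2 × 11.6² × (1.960 + 0.842)² / 12² = 14.7, so 15 (normal approximation) or 16 (t-test).
- The stated 20 does not follow from the stated inputs. It would follow from 90% power (19.6, so 20, by the normal approximation) or from α = 0.025 with 80% power by the t-test (20).
- At 20 per arm and α = 0.05, power for SDM-Q-9 is 90.5% (normal) or 89.0% (t-test).

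**Step 2. Familywise error if either primary may be claimed.** For independent tests, 1 − 0.95² = 9.75%, which is 1.95 times 5%. For correlated tests it is 1 − P(|Z₁| < 1.96 and |Z₂| < 1.96), with Z₁ and Z₂ bivariate normal:

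| ρ (assumed) | Familywise error |
|---|---|
| 0 | 9.75% |
| 0.3 | 9.5% |
| 0.5 | 9.1% |
| 0.7 | 8.3% |
| 0.9 | 7.0% |

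**Step 3. If both must be significant.** The chance of falsely declaring joint success is at most 5%. With no effect on either outcome and independent tests, it is 0.05² = 0.25%. There is no inflation. Joint power depends on the STAI-6 effect and standard deviation, which are not given. As an illustration only, if STAI-6 had the same power as SDM-Q-9 at 20 per arm and the tests were independent, joint power would be 0.905² = 81.9% (normal) or 0.890² = 79.2% (t-test).

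**Step 4. Cost of stricter testing.** The strictest level SDM-Q-9 could face under Holm is 0.025.

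- n = 2 × 11.6² × (2.241 + 0.842)² / 12² = 17.8, so 18 per arm (normal).
- By the t-test, power is 77.2% at 18, 79.8% at 19 and 82.1% at 20, so 20 per arm are needed.
- At the planned 20, power is 84.8% (normal) or 82.1% (t-test).

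All of these sample-size and power figures ignore clustering by surgeon, as the protocol's own calculation does.

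**The case against.** **Either-wins is not stated.** The only wording on joint success, in the primary hypothesis, uses 'and', and a both-must-win rule has no inflation. This stands, so the near-doubling is conditional. But the hypothesis is not made a decision rule. Read literally, it would also require an outcome that the outcome list makes secondary.

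**Multiplicity is commonly left to the SAP, and this is a pilot.** The absence of a procedure would not by itself be a finding. Here the protocol does fix a level for every test, so an SAP that adjusted the primaries would depart from it. The mismatch between Specific Aims and Outcome Measurements also lies within this one document. Pilot status lowers the stakes, but Trial Design also calls the trial a superiority trial, and the sample-size text claims adequate power.

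**Stronger readings that the document does not support.**

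- A reader might count all three parts of the hypothesis and quote 1 − 0.95³ = 14.3%. That treats a secondary outcome as a primary success and needs three independent tests under an any-wins rule.
- A reader might say that power under an all-must-win rule is lower than the stated 80%. This is not shown: there are no STAI-6 inputs, and the illustration in the working lands close to 80%.
- A reader might add further inflation from how the restricted maximum-likelihood model is tested. The protocol states no reference distribution or degrees-of-freedom method, and that is a separate question.
- A reader might infer from the 20 per arm that alpha was already split. 90% power explains the figure equally well, and either explanation conflicts with the stated error rates.

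**Conclusion.** The point holds in conditional form. The protocol states a 5% type I error, names two primary outcomes, tests each at 0.05 and gives no success rule. Under an either-wins reading the familywise error is between 7.0% and 9.75% for correlations from 0.9 down to 0, and at least 9.1% for correlations up to 0.5. These figures assume two-sided tests that each hold their nominal 0.05. Under a both-must-win reading the 5% is kept, and the gap is that power for the joint claim has not been established. It does not follow that the trial's error rate is nearly double whatever rule is used. The rule should be fixed before analysis; the trial remains interpretable if that is done.

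**What to change.** In Statistical Considerations, replace the flat 0.05 for the two primaries with Holm at a familywise 0.05: the smaller p-value is tested at 0.025 and, if that succeeds, the other at 0.05. Two alternatives are equally sound if written down in advance:

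- declare that both primaries must be significant at 0.05; or
- name SDM-Q-9, the outcome used for sizing, as the lead primary, and test STAI-6 at 0.05 only if SDM-Q-9 succeeds.

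The choice belongs to the sponsor; lowering the rank of STAI-6 is not a necessary correction. Also bring the primary hypothesis in Specific Aims into line with Outcome Measurements on whether understanding is primary or secondary.

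The cost is wording in these sections and slightly stricter testing. Under Holm, SDM-Q-9 still fits the planned 20 per arm on the protocol's unclustered inputs, though by the t-test it leaves no spare patients. Under the fixed sequence, a STAI-6 claim is lost if SDM-Q-9 fails. Under the both-required rule, one significant result alone supports no primary claim. The effect of any option on STAI-6 power cannot be computed until the protocol gives a STAI-6 target effect and standard deviation.

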## Record Retention and Access to Data

This study is expected to complete recruitment within 8 weeks of initiation. The study PI may retain all data records indefinitely (as per institutional policy). Other investigators will not have access to the trial data after the study is completed.

## Limitations of Study

Since this is a single-center and single-specialty study, the results might not be generalizable to other surgical fields and centers. Secondly, the results of this study will only be applicable to patients fluent in the English language owing to the language and validation of the scales used.

